Onsite medication treatment at SSPs has improved pharmacologic adherence and subsequently health outcomes for PWID [25, 26]. Variations of onsite HCV treatment colocated at SSPs may bundle testing, phlebotomy, and medication distribution. These studies report high rates of uptake and more than 89% of patients achieving sustained virologic response [26, 27]. One low-barrier onsite buprenorphine treatment program reported one-third of SSP participants continuing MOUD for 180 days or more [25]. Treatment retention among PWID with HIV on MOUD is significant compared to those not on MOUD, as one non-SSP systematic review and meta-analysis found that MOUD was associated with a 69% increase in ART initiation, 2-fold increase in adherence, and 45% increase in odds of HIV viral suppression [28].

Telehealth harnessed during the COVID-19 pandemic improved the treatment gap for people with HIV who use drugs, decreasing barriers of transportation and expanding outreach to remote communities, especially those experiencing homelessness [29, 30]. For people with HIV, telehealth helped providers overcome many of the factors described as barriers to care, including fear of judgement in face-to-face consultations and concerns of privacy and confidentiality [31]. Emergency regulatory changes waived the in-person clinician visit for buprenorphine prescribing, allowing for low-barrier telehealth-enhanced harm reduction interventions to be delivered to sites often frequented by PWID, including SSPs [29]. One SSP-centered telehealth model [32] offered successful co-treatment for HIV, substance use disorder, and HCV with similar rates of SVR as treatment colocated on site at an SSP [26]. However, currently no trials exist that focused on achieving viral suppression with PWID with HIV by employing a harm reduction approach in the setting of an SSP.

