### Outcomes {12}

Table 1 shows the outcomes.

**Table 1 Tab1:** Outcomes

Primary outcomes	Definition	Measure
Viral suppression	HIV viral load <200 copies/ml	HIV viral load <200 copies/ml time-averaged over 3, 6, and 12 months post baseline
Secondary outcomes	Definition	Measure
Initiation of MOUD	Receiving prescription and taking first dose of buprenorphine, naltrexone, or methadone	Positive UDS for buprenorphine, naltrexone, or methadone at study follow-up visit after MOUD is prescribed
HCV cure	Achieving 12-week sustained virologic response	HCV treatment initiated resulting in negative HCV RNA at 12 weeks post treatment completion
Cost-effectiveness	Cost per unit of a desired outcome (e.g., cost per viral suppression; cost per HCV cure)	Incremental cost-effectiveness ratios (ICERs) over 3, 6, and 12 months post baseline.

The primary trial outcome is HIV viral suppression. Viral suppression will be defined as HIV RNA <200 copies/ml which will be time-averaged HIV viral suppression over 3-, 6-, and 12-month follow-up. Secondary outcomes include initiation of MOUD defined as receiving a prescription and taking first dose of buprenorphine, naltrexone, or methadone. MOUD initiation will be measured by UDS positive for buprenorphine, naltrexone, or methadone at study follow-up visit at 3, 6, or 12 months. An additional secondary outcome is HCV cure, defined as achieving 12-week sustained virologic response. HCV cure will be measured by negative HCV RNA at 12 weeks post treatment completion.

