#### Data analysis plan and statistical procedures to address secondary hypotheses

For preliminary analyses and missing data, the secondary analyses will use the same preliminary analysis and missing data strategy as Hypothesis 1. Hypothesis 2 is that *THR* will be superior to off-site linkage to HIV care in achieving (1) initiation of MOUD and (2) retention in MOUD as evidenced by positive UDS for MOUD. Hypothesis 3 is that *THR* will be superior to off-site referral and off-site linkage to HIV care in achieving (1) initiation of medication (DAA) for HCV Cure and (2) HCV cure as evidenced by undetectable HCV RNA at 12 weeks post HCV treatment (SVR12).

Hypotheses 2a and 3a will be tested using a logistic regression model where the dependent measure is equal to zero if the individual does not initiate the medication prior to the end of the study (month 12) and is equal to 1 if the individual does initiate the medication prior to the end of the study. We will test whether *THR* relative to the control group increases the odds of initiating the respective medication. Note that for Hypothesis 2a the sample is all participants, whereas, for 3a, it is only those eligible for HCV treatment, i.e., who have a positive HCV viral load at baseline.

Hypotheses 2b will be tested as will be Hypothesis 1, with GEE as a time-averaged comparison of post-initiation of MOUD measurements of presence of MOUD by UDS between those randomized to *THR* and the control condition. To maintain this hypothesis test as an intention to treat analyses, in the initial test, all participants will be included. Those who have not initiated will be coded as not retained. In a planned post hoc comparison, the sample will be reduced to only those who have initiated to examine whether there is a difference in rates of retention conditional on initiation.

Hypothesis 3b will be tested as will be H2a and H3a using logistic regression. Initial intent-to-treat analyses will compare the odds of achieving HCV cure in the 12 months post randomization within the *THR* arm relative to the control arm within the full sample that was HCV positive at baseline. Planned post hoc comparisons will repeat this analysis within the sample that initiated HCV treatment to examine whether there were significant differences conditional on initiation.

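### Hypothesis 2b scores MOUD retention only on visits after initiation, so the number of visits counted depends on when treatment starts and a later-starting arm is flattered

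*Protocol article*

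**What the plan says.** Protocol article, data analysis plan for the secondary hypotheses: Hypothesis 2b is to be tested in the same way as Hypothesis 1, with "GEE as a time-averaged comparison of post-initiation of MOUD measurements of presence of MOUD by UDS". To keep the comparison intention-to-treat, "in the initial test, all participants will be included", and "Those who have not initiated will be coded as not retained". A planned post hoc comparison is limited to initiators.

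The text does not say whether a late initiator's visits before starting are left out or scored 0. It also does not say whether initiation is dated by prescription or by first positive UDS.

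For Hypothesis 2a, the outcome "is equal to 1 if the individual does initiate the medication prior to the end of the study". The Outcomes section defines initiation one way ("Receiving prescription and taking first dose of buprenorphine, naltrexone, or methadone") and measures it another: "MOUD initiation will be measured by UDS positive for buprenorphine, naltrexone, or methadone at study follow-up visit at 3, 6, or 12 months". Table 1 adds that the positive screen must follow a prescription.

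**The concern.** Coding never-initiators as failures settles their case, but not that of people who start late. If only visits after initiation count, a participant who starts in month 11 and is positive at month 12 contributes one visit, a success. One who starts in week 1, is positive at month 3 and then stops contributes three visits, one of them a success. The first is scored 100% and the second 33%, although the second was tested positive just as often.

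The denominator is therefore set by time to initiation, which treatment may affect. THR offers MOUD repeatedly within the intervention, while control participants obtain it from an off-site clinic, so earlier starts under THR are plausible. At stake is a superiority test with its own alpha of 0.05 that may understate THR's effect on time on MOUD. The primary viral-suppression analysis is not touched.

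Hypothesis 2a has a smaller, separate problem: someone who starts and stops between visits meets the definition and fails the measure.

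**Working it through.** The article gives no expected rate or power for Hypotheses 2a or 2b. Its 15-point detectable difference is for the primary outcome, so there is no plan figure to reproduce here.

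**Inputs from the article.** Visits at months 3, 6 and 12; all participants included; never-initiators score three zeros. Persistence: one onsite buprenorphine programme "reported one-third of SSP participants continuing MOUD for 180 days or more" (Background).

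**Assumptions.** Half of each arm initiates (p = 0.5). Stopping is exponential, equal in both arms, without restarts. UDS is positive exactly while on MOUD. No visits are missed. 180-day persistence S is 1/3, with 1/2 and 2/3 as a range. THR starts are uniform over months 0–1; control starts are uniform over the windows in the table. GEE is approximated by the pooled visit proportion (working independence).

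**Step 1, stopping rate.** λ = −ln(S)/5.91 per month (180 days = 5.91 months): 0.186, 0.117, 0.069.

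**Step 2, positive visits per initiator (k).** For starts uniform on (a, b) and a visit v ≥ b, the probability of being on MOUD is [e^(−λ(v−b)) − e^(−λ(v−a))]/[λ(b−a)]. For a visit inside the window, only starts up to v count. Summing over visits gives k. THR: k = 1.108, 1.531, 1.983. Control, starts over 0–12: k = 0.893, 1.106, 1.317.

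**Step 3, the two scores.** Let m be the mean number of visits at or after the start.
- All visits: p·k/3.
- Post-initiation only: p·k/[p·m + 3(1−p)].
- Ratio: 3/[3 − p(3−m)]. It is never below 1 and does not depend on persistence.

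Example, control 0–12 at S = 1/3: 0.5×0.893/3 = 14.9%; 0.5×0.893/(0.5×1.75 + 1.5) = 0.4465/2.375 = 18.8%.

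THR (m = 3) scores 18.5%, 25.5% and 33.0% under both rules. Control, all-visit → post-initiation (gain in points):

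| Control starts, months | m | Ratio | S = 1/3 | S = 1/2 | S = 2/3 |
|---|---|---|---|---|---|
| 0–3 | 3 | 1.00 | 22.5 → 22.5 (0) | 28.8 → 28.8 (0) | 35.4 → 35.4 (0) |
| 0–6 | 2.5 | 1.09 | 19.7 → 21.5 (1.8) | 24.9 → 27.2 (2.3) | 30.2 → 33.0 (2.7) |
| 3–6 | 2 | 1.20 | 17.0 → 20.4 (3.4) | 21.0 → 25.2 (4.2) | 25.0 → 30.1 (5.0) |
| 0–12 | 1.75 | 1.26 | 14.9 → 18.8 (3.9) | 18.4 → 23.3 (4.9) | 22.0 → 27.7 (5.8) |
| 6–9 | 1 | 1.50 | 7.3 → 11.0 (3.7) | 9.9 → 14.8 (4.9) | 12.3 → 18.4 (6.1) |

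**Step 4, THR minus control.** With control starts over 0–12, the difference goes from 3.6 to −0.3 points (18.5−14.9; 18.5−18.8), from 7.1 to 2.2, and from 11.0 to 5.3. The sign also changes for starts over 3–6 at S = 1/3 (1.5 to −1.9) and over 0–6 at S = 1/2 (0.6 to −1.7). Elsewhere it does not change.

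**Step 5, initiation dated by first positive UDS.** Undetected starters become three zeros, and detected ones count from the first positive visit. For control 0–12 at S = 1/3, starts in months 0–3 and 3–6 are each detected with probability 0.767, and starts in 6–12 with 0.603 (0.685 overall). Denominator: 0.5×(0.25×0.767×3 + 0.25×0.767×2 + 0.5×0.603×1) + 3×(1 − 0.5×0.685) = 0.630 + 1.973. Score: 0.4465/2.603 = 17.2%, against 18.5% for THR. The control gain falls from 3.9 to 2.3 points.

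**Step 6, Hypothesis 2a.** A start at time s is detected at the next visit v with probability e^(−λ(v−s)). For THR this averages 62.9%, 74.6% and 84.3%, so 37%, 25% and 16% of starters are missed. At S = 1/3, control detection is 68.5% for starts over 0–12 but 43.9% for starts over 6–9. With true initiation of 50% in both arms, UDS-defined initiation is then 31.5% vs 34.2%, or 31.5% vs 21.9%: the direction flips.

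**The case against.** The strongest reply is that the rule examined here is only one reading. Hypothesis 2b is to be tested as Hypothesis 1 is, and that analysis uses all three visits. If the coding of non-initiators applies visit by visit, a late starter's earlier visits score 0 and nothing is lost. The article condenses a fuller plan, and the final analysis plan is to be confirmed before data lock.

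This stands in part: the per-visit reading is possible and would remove the problem. But the article itself names the measurements that enter the model, and restricting them to those after initiation has no effect on late starters unless their earlier visits are dropped. One sentence would settle it.

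A reader might infer more: that both MOUD tests are biased against THR, and that a real benefit will vanish or reverse. The documents do not support that. No time to initiation is given for either arm, and faster starts under THR are an inference from how MOUD is offered. In Hypothesis 2a the direction is not fixed, because the six-month gap before month 12 can miss more late control starters than early THR starters. In Hypothesis 2b the sign changes in only some scenarios, and the persistence figure comes from a single buprenorphine programme.

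It is also fair to say that UDS is an objective measure applied alike in both arms of an open-label trial. Replacing it with prescription records would risk unequal ascertainment, since study clinicians prescribe in one arm and off-site clinics in the other.

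**Conclusion.** The concern holds for Hypothesis 2b in limited form. Read plainly, the post-initiation restriction makes the denominator depend on a post-randomisation event, so the test is not the intention-to-treat comparison the article says it maintains. Compared with all-visit scoring, it can only raise an arm's score. Under the assumptions above, a later-starting control arm gains about 2 to 6 points when some or all of its starts fall after month 3, nothing when all fall before month 3, and less under UDS dating. For scale, the article's detectable difference for its primary outcome is 15 points. A THR advantage can shrink; the documents cannot show whether it would reverse.

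The mismatch between definition and measure in Hypothesis 2a is real and misses about 16% to 37% of early starters across the persistence range. It calls for accurate labelling, not a new main measure.

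**What to change.** **Hypothesis 2b.** State that all three scheduled visits (months 3, 6 and 12) are scored for every randomised participant, UDS positive for MOUD as 1 and otherwise 0, whenever MOUD began. Keep the initiators-only comparison as post hoc. This needs wording only and no new data. The test then measures being on MOUD across follow-up, combining starting and staying, and should be described so. The wording should also say whether Table 1's requirement of a preceding prescription applies to these visits.

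**Hypothesis 2a.** Keep UDS as the main measure and describe the outcome as MOUD detected at a follow-up visit, so that definition and measure agree. Add initiation by prescription and first-dose records as a sensitivity analysis only, from the same sources in both arms. The cost is abstraction of off-site records, for which every participant already signs a release.

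### The supplementary initiators-only comparisons of MOUD retention and HCV cure are not protected by randomisation and should be reported as descriptive; the main intention-to-treat tests of 2b and 3b stand

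*Protocol article*

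**What the plan says.** All of this is in the Protocol article, under the data analysis plan for the secondary hypotheses.

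- **Initiation is a hypothesised effect.** Hypotheses 2a (MOUD) and 3a (DAA) are tested by asking whether THR "relative to the control group increases the odds of initiating the respective medication". The Objectives section likewise expects THR to increase uptake of both.
- **Main test of 2b (MOUD retention).** "To maintain this hypothesis test as an intention to treat analyses, in the initial test, all participants will be included". For the remainder, "Those who have not initiated will be coded as not retained".
- **Main test of 3b (HCV cure).** Logistic regression comparing the arms "within the full sample that was HCV positive at baseline".
- **Supplementary repeat for 2b.** In a comparison labelled planned and post hoc, "the sample will be reduced to only those who have initiated to examine whether there is a difference in rates of retention"; the sentence goes on to say that this is conditional on having started.
- **Supplementary repeat for 3b.** The cure analysis is run again "within the sample that initiated HCV treatment to examine whether there were significant differences conditional on initiation".

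Alpha of 0.05 is assigned to 2a, 2b, 3a and 3b. The initiators-only repeats get no alpha of their own. The article does not call them descriptive and describes no method for selection into initiation.

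**The concern.** The repeats compare arms within a subset defined by an event that follows randomisation and that the intervention is designed to change. If THR succeeds on 2a or 3a, its starters include people who would not have started under off-site linkage. Control starters include no such people unless off-site linkage also draws in some who would not start under THR. The two groups then differ for reasons other than the effect of arm on retention or cure.

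Two conditions are needed: initiation must differ by arm, and it must be related to later retention or cure. The first is the trial's own hypothesis. The second is plausible but not established. The moderation section plans to relate syndemic factors to engagement in MOUD and HCV treatment, and expects THR to lessen their impact. THR may therefore draw in people with more barriers to staying on treatment.

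At stake is how two secondary results are read. Someone asking whether THR keeps people on treatment once started will look at the initiators-only result. If added starters are harder to retain, that result could suggest that THR retains or cures worse when it does not.

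**Working it through.** **Plan's own figure.** There is none to reproduce. The article gives no initiation, retention or cure rates by arm and no power for these comparisons. Its 15-point minimum detectable difference concerns the primary outcome only.

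**Inputs from the article.** 240 participants, evenly assigned, so 120 per arm. HCV prevalence of 55.2% among people who inject drugs (Background), taken here to apply to the trial: 0.552 × 240 / 2 ≈ 66 per arm. Cure above 89% in cited studies of HCV treatment at syringe services programs (Background), used as an illustrative control value. Everything else below is assumed.

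**Step 1: mixture arithmetic, no effect of arm on retention.** Let p0 and p1 be the initiation rates (control, THR), with everyone who would start under control also starting under THR. The share of THR starters who would start in either arm is s = p0/p1. With retention A in those people and B in those who start only under THR:

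- control starters: A
- THR starters: s·A + (1 − s)·B
- spurious difference: (1 − s)(B − A)

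Take p0 = 0.30 and p1 = 0.50, so s = 0.60, and A = 0.60.

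- B = 0.40: THR = 0.60 × 0.60 + 0.40 × 0.40 = 0.52 against 0.60, a difference of −8 points.
- B = 0.30: THR = 0.60 × 0.60 + 0.40 × 0.30 = 0.48 against 0.60, a difference of −12 points.
- If s = 1 (equal initiation) or B = A (initiation unrelated to retention), the difference is zero.

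**Step 2: would a test pick it up?** Starters number 0.30 × 120 = 36 and 0.50 × 120 = 60. For a single measurement, SE = √(0.60 × 0.40/36 + 0.52 × 0.48/60) ≈ 0.104, so z ≈ 0.08/0.104 ≈ 0.8. A two-sided 5% test rejects about 12% of the time. For the 12-point case it rejects about 21%.

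**Step 3: check with a second model.** Initiation and retention are each driven by a normal latent variable, with correlation r between the two. The retention threshold is the same in both arms. Retention is set at 50% in control starters, with 120 per arm and a two-sample test of proportions.

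| Initiation, control vs THR | r | Retention in starters, control vs THR | Rejection at nominal 5% |
|---|---|---|---|
| 30% vs 30% | 0.5 | 50% vs 50% | 5.0% |
| 30% vs 60% | 0 | 50% vs 50% | 5.0% |
| 30% vs 50% | 0.5 | 50% vs 42.1% | 11.6% |
| 30% vs 60% | 0.3 | 50% vs 43.7% | 9.6% |
| 30% vs 60% | 0.5 | 50% vs 39.0% | 19.5% |
| 30% vs 60% | 0.7 | 50% vs 33.3% | 38.8% |

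Simulation (20,000 runs) gave 9.8% at r = 0.3 and 19.7% at r = 0.5 for 30% vs 60%.

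**Step 4: HCV cure.** Same model, 66 per arm, 89% cure in control starters, initiation 30% vs 60%, r = 0.5: 89% vs 82%, with rejection of 9.0% (7.8% by simulation). The corresponding retention case gives an 11-point gap and 19.5%.

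**Step 5: what the data could say about the same people.** In the 52% case of Step 1, s = 0.60. THR retention in those who would start in either arm is then bounded by (0.52 − 0.40)/0.60 = 0.20 and 0.52/0.60 ≈ 0.87. This needs the assumption that nobody starts under control who would not start under THR.

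**The case against.** The strongest reply is that the plan is already built correctly. The alpha-bearing tests of 2b and 3b use all participants and all who were HCV positive at baseline. The repeats come second, are labelled post hoc, and are openly described as conditional. This stands. A reader might infer that retention and cure are tested only in starters, or that the secondary hypotheses are biased, but the article says the opposite.

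Three further limits also stand.

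- A reader might infer that significance is sought in both repeats. That word appears only in the HCV sentence; the MOUD sentence speaks of a difference in rates.
- A reader might infer that a false finding is likely. No rates are given, and under the Step 1 rates most trials would show no significant difference. Nor is the direction fixed: it runs against THR only if added starters do worse.
- MOUD retention is a stated hypothesis but is not among the outcomes in Table 1, so its repeat supplements a measure already in second place.

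The label does not settle the matter, though. Neither the post hoc label nor the planned adjustment for site addresses who ends up among the starters. The intention-to-treat test of 2b does not make the repeat redundant either, because coding non-initiators as not retained combines initiation with retention. In the Step 3 model with 30% vs 60% and r = 0.5, it compares 0.30 × 0.50 = 15.0% with 0.60 × 0.390 = 23.4% and rejects 37.7% of the time with no arm effect on retention itself. That is a valid randomised contrast, but it does not isolate retention, so readers will turn to the repeat for an answer.

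**Conclusion.** The point holds for the two supplementary comparisons only, and its severity is minor. The primary analysis and the main tests of 2b and 3b are unaffected.

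If THR raises initiation and willingness to start is related to later outcome, the initiators-only contrast can differ from zero with no effect of arm. Under the assumed rates the gap for retention is 8 to 12 points, and in the second model the false-positive rate runs from about 10% to 39% when initiation doubles from 30% to 60% and r is 0.3 to 0.7. For HCV cure the inflation is modest, about 8% to 9% at r = 0.5. If either condition is absent, the rate stays at 5%. These sizes are illustrations, because the documents give no rates from which to estimate the bias.

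**What to change.** In the section on the secondary hypotheses, replace the two planned post hoc comparisons with a statement along these lines: retention among MOUD starters and cure among DAA starters will be given as percentages by arm; these are descriptive and not a randomised comparison; no p-value or superiority statement will accompany them; conclusions on 2b and 3b rest on the intention-to-treat tests.

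If an answer for people who would start in either arm is wanted, bounds can be added from the same data, with the one-directional initiation assumption stated. That assumption is not self-evident here, since controls get an accompanied handoff to clinics that provide both treatments. The bounds may also be wide (20% to 87% in the example), so they are optional.

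The cost is a change of wording and the loss of significance testing in two supplementary repeats. No new data are needed and the main tests do not change. The change can be made when the analysis plan is confirmed before data lock, as the article foresees.
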